#### Process evaluation

In addition, process evaluation indicators are also measured. The main components in process evaluation are contamination (e.g., ‘Have you subscribed to other information resources that provide HIV- or ART-related information?’ and ‘Have you ever consulted the research team’s WeChat account?’) and the usage of mHealth intervention (e.g., ‘Have you ever initiated online communication with case managers/read delivered articles/searched for articles of interest within the WeChat platform?’, ‘What topics have you consulted your case managers about?’, and ‘How frequently do you use this WeChat platform?).

Participants will also be asked to provide an overall comment about the extent to which the platform helps in their daily life. Qualitative interviews will be conducted with the four nurse case managers to investigate the feasibility and acceptability of design and implementation of the intervention. Objective process evaluation indicators will be retrieved from the intervention APP, including the number of times each educational article has been read, the number of enrolled patients for each case managers, the numbers of days when case managers had conversation with patients, and the total numbers of messages sent by case managers. In addition, with the consent of participants, the frequency of key words emerging in the conservation will be counted, to identify the top priority of patients during the initial ART phase.

### Sample size estimation

We will calculate the size of effect that the sample size in our study can detect with 80% power (two-tailed alpha 0.05) with regard to the primary outcome. Based on previous studies conducted among Chinese MSM that newly initiate ART, we estimate that the adherent rate at month six in the control group will be 89% [14]. The target sample size of 600 (300 in each arm) will be powered to detect a smallest between-group difference of 9% in adherent rates, allowing for a 20% attrition rate at month six.

### Data storage and management

All paper documents, including informed consents, service contracts and notebooks of enrolment information will be stored in a locker in the principal investigator’s office at Sun Yat-sen University. Digital data will be retrieved after the study period, stored on a password-protected computer, and deleted permanently from the ‘Trusted Doctor’ server. To preserve confidentiality, all direct personal identifiers will be removed and replaced with a RID in the data files, which will also be protected with a password. Only persons who are part of the research team will have access to the data. Nurses’ APP accounts and investigators’ WeChat accounts are password-protected for exclusive use in this study. No personal information will be documented on the investigator’s WeChat contact; each participant who friends an investigator will be given their RID as a WeChat alias.

### Statistical analysis

#### Baseline comparison

The equivalence between the baseline characteristics of the two arms will be analysed by calculating the standard difference (SDiff). A value > 0.1 will reveal imbalance.

#### Effectiveness of intervention

The primary outcomes will be the prevalence of ART adherence and CD4 counts at month six. For the between-group comparisons, *χ*^*2*^ test will be used for binary outcomes (e.g., ART adherence, mental health disorders, sexual risk behaviours) and *t*-test for continuous outcomes (e.g., CD4 count, quality of life, illness representation, IMB constructs, and HIV viral load). Within-subject analyses will also be conducted, comparing the baseline response to follow-up session responses.

Intervention effects will be performed on the principle of intention-to-treat (ITT), using the data collected from all randomized participants in the analysis. Missing endpoints will be imputed by Multiple-Imputation approach. The General estimating equation (GEE) will be used for repeated measures analyses using SAS 9.0, which allows for the inclusion of all subjects in the analysis regardless of their number of visits. As GEEs require data to be randomly missing, the analysis will be repeated using a subset of participants with complete data. A sensitivity analysis will be conducted to determine the impact of dropout and to evaluate additional longer timeframes (month 12).

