### Data collection

Baseline assessment is initially being conducted at the enrolment procedure on a tablet, under the instruction of investigators. Data on demographic characteristics (age, marital status, education, monthly income, employment, and eHealth literacy), HIV status (transmission route, duration after diagnosis, sexual orientation, sero-status disclosure, STDs), psycho-social conditions (mental health, quality of life, illness representation, perceived stigma, social support, IMB constructs) and risky behaviours (sexual and drug use behaviours) are collected.

Follow-up assessments will be scheduled at months 1, 3, 6 and 12 (6-month post-intervention). The content of follow-up assessments at each time-point is described in Table 3, and covers variables related to ART adherence, mental health, illness representation, sexual risk behaviour, IMB constructs and quality of life. The links to the online questionnaire will be sent to all participants automatically via WeChat, and they can fill in the questionnaire on any electronic device, such as smartphones. Questionnaires are checked weekly and reminder messages are sent to participants who have not completed the questionnaires in the required time. If the reminders have been sent twice and ignored twice, a phone call will be made to participants. Participants can receive an online cash transfer of 10 Chinese Yuan (CNY), 20 CNY and 20 CNY (50 CNY in total, which equals approximately 7 US dollars) if they finish the follow-up questionnaires in each of months 3, 6 and 12.

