#### Secondary outcomes

***HIV-1 RNA*** viral load at month 12 was measured by polymerase chain reaction (PCR).

***Mental health*** status includes anxiety and depression, which are measured by the seven-item Generalized Anxiety Disorder-7 (GAD-7) instrument [48] and nine-item Patient Health Questionnaire-9 (PHQ-9) [49], respectively. Both instruments comprise four-point Likert scales with the responses based on occurrence of symptoms during the last week. In each scale, the sum of all items will be calculated and categorized into different levels of mental health disorder: normal (0–4), mild (5–9), moderate (10–14), and moderate to severe (≥15) [50, 51].

***Quality of life*** is measured by the 31-item HIV adaptation of the World Health Organization Quality of Life scale (WHOQOL-HIV bref) [52], which has shown good reliability and validity among Chinese PLWHA [53]. The scale consists of six domains: physical health, level of independence, psychological health, spirituality, social relations and environmental health. For each domain, a score ranging from 4 to 20 will be calculated, with higher scores denoting better quality of life.

***Illness representation*** is measured by the Brief Illness Perception Questionnaire (B-IPQ), which has been used among PLWHA to evaluate their cognitive and emotional response towards HIV [54]. The B-IPQ comprises the following eight dimensions: consequences, timeline, personal control, treatment control, identity, coherence, concern, and emotional response. Each dimension has only one question, with responses rated on a scale from 0 to 10. A higher score indicates a greater perception of a threat from HIV [55].

***ART-related perception*** is measured by the Life Windows Information-Motivation- Behavioural Skills ART Adherence Questionnaire (LW-IMB-AAD) [56]. The instrument consists of 33 items rated on a 5-point Likert scale, with nine measuring information, ten measuring motivation, and 14 measuring behavioural skills. Summative scores are computed for each aspect, with higher scores reflecting better information, motivation and behavioural skills about adherence [57].

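### The between-group test named for depression and anxiety is a chi-square on a binary outcome; a baseline-adjusted analysis of the PHQ-9 and GAD-7 sum scores would use more of the data at almost no cost

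*Protocol article*

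**What the plan says.** Under Secondary outcomes, anxiety (GAD-7) and depression (PHQ-9) are scored in two steps: "the sum of all items will be calculated and categorized into different levels of mental health disorder". The levels are "normal (0–4), mild (5–9), moderate (10–14), and moderate to severe (≥15").

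Under Effectiveness of intervention, the chi-square test "will be used for binary outcomes (e.g., ART adherence, mental health disorders, sexual risk behaviours"). The t-test is "for continuous outcomes (e.g., CD4 count, quality of life, illness representation, IMB constructs, and HIV viral load"). The PHQ-9 and GAD-7 sums are not among the t-test examples, although the other questionnaire scores are.

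The same section adds a longitudinal model: "The General estimating equation (GEE) will be used for repeated measures analyses using SAS 9.0". It does not say whether PHQ-9 and GAD-7 enter that model as sums, levels or a binary variable.

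Under Data collection, the baseline assessment covers "psycho-social conditions (mental health, quality of life, illness representation" and further scales), so a baseline value of each score should be available.

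**The concern.** Four ordered levels, and the sum behind them, are reduced to two categories before the arms are compared. Two men who score 5 and 20 count as the same if the cut is at 5; two who score 4 and 5 count as different. The other questionnaire scores are spared this, and the article gives no reason for treating depression and anxiety differently.

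A simple chi-square also takes no account of where each man started. Men newly starting ART are likely to differ widely in baseline distress, and adjusting for it usually narrows the interval.

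What is at stake is precision on two named secondary outcomes. A non-significant chi-square could be read as no effect on mental health when the sum score, already computed, would have given a clearer answer.

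**Working it through.** **Figures in the plan.** There is nothing to reproduce for these scales: the article gives no SD, prevalence, effect size or cut-off for PHQ-9 or GAD-7. Its one design calculation concerns adherence ("can detect with 80% power (two-tailed alpha 0.05) with regard to the primary outcome"). Only the sample size is taken from it: 300 per arm with 20% attrition leaves 300 × 0.80 = 240 per arm.

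**Step 1: binary split against the sum score.** Assume the score is roughly normal and the intervention shifts its mean. With a proportion *p* above the cut and *z* the matching normal quantile, the efficiency of the binary comparison relative to a t-test on the score is RE = φ(z)² / [p(1 − p)]. The splits are assumptions.

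| *p* above cut | RE | Loss | 240 per arm act like | 300 per arm act like |
|---|---|---|---|---|
| 0.50 | 0.637 | 36% | 153 | 191 |
| 0.30 | 0.576 | 42% | 138 | 173 |
| 0.20 | 0.490 | 51% | 118 | 147 |
| 0.10 | 0.342 | 66% | 82 | 103 |

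RE is greatest at *p* = 0.50, so about 0.64 is the ceiling under this model.

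**Step 2: does this depend on normality?** PHQ-9 and GAD-7 are usually skewed. Negative-binomial scores with means of 4 to 8 and dispersion 0.7 to 2, with a proportional change in the mean and cuts at 5 or 10, gave losses of 35% to 57% against the t-test. The order of magnitude stays the same.

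**Step 3: binary split against the four levels.** For assumed level distributions and the same normal shift, the further loss is 1 − RE(binary)/RE(four levels).

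| Levels (%) | RE four levels | RE cut ≥5 | RE cut ≥10 | Further loss ≥5 | Further loss ≥10 |
|---|---|---|---|---|---|
| 50/30/12/8 | 0.785 | 0.637 | 0.490 | 19% | 38% |
| 60/25/10/5 | 0.724 | 0.622 | 0.426 | 14% | 41% |
| 40/30/20/10 | 0.834 | 0.622 | 0.576 | 25% | 31% |
| 70/20/7/3 | 0.640 | 0.576 | 0.342 | 10% | 47% |

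Against the levels, then, the loss is about 10–25% for a cut at 5 and about 31–47% for a cut at 10.

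**Step 4: what it means for power.** With 240 per arm, two-sided 0.05 and an assumed true shift of *d* SD:

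| *d* | t-test on sum | Binary, 50% | Binary, 30% | Binary, 20% |
|---|---|---|---|---|
| 0.20 | 59.1% | 41.3% | 36.8% | 31.5% |
| 0.25 | 78.2% | 58.5% | 52.2% | 44.7% |
| 0.30 | 90.8% | 74.1% | 67.1% | 58.3% |

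**Step 5: baseline.** If baseline and follow-up scores correlate at *r*, adjustment reduces the residual variance by the factor 1 − r². At *r* = 0 nothing is gained. At an assumed *r* = 0.5 the factor is 0.75, so the unadjusted binary test has efficiency 0.637 × 0.75 = 0.48, 0.576 × 0.75 = 0.43 and 0.490 × 0.75 = 0.37 relative to the adjusted score. The article gives no value for *r*.

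**The case against.** A reader might infer that the two sections contradict each other. They do not. The scoring section labels 0–4 as normal and calls the bands levels of disorder, so any disorder against normal follows directly from it. The article treats adherence in the same way: a 0–100 score is computed and then dichotomised.

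A reader might also infer that the sums will never be analysed. The text does not go that far. The lists of outcomes are introduced as examples, GEE is planned without limiting it to binary variables, and the structural equation models include psychosocial health outcomes. What stands is that no section states the scale used for PHQ-9 and GAD-7 in those models, and the one test tied to mental health is the chi-square.

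The binary cut is not named, and cuts at 5, 10 and 15 all fit the four levels. For a secondary outcome that detail is commonly left to the analysis plan, which is not shown, so its absence is not counted here. Naming the cut would settle the definition but would not recover the discarded information.

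The baseline argument is not special to these scales: the t-tests on CD4 and quality of life also omit baseline. The article does plan within-subject comparisons of baseline with follow-up, but these do not adjust the difference between arms.

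Finally, a disorder rate is easy to interpret. A binary endpoint fixed in advance loses power but does not bias the test or raise its type I error. All of that stands.

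**Conclusion.** The point holds as a matter of efficiency. The article states a less precise between-group method for PHQ-9 and GAD-7 than its own data allow, and a less precise one than it uses for its other questionnaire scores.

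The size depends on the comparator. Against the sum score under a normal shift, relative efficiency is at most about 0.64, falling to 0.58 and 0.49 if 30% and 20% are above the cut; the skewed checks agree broadly. It would be wrong to state a loss of a third or more without these conditions. Against the four levels, a cut at 5 loses only about 10–25%. The split proportions, level distributions, effect sizes and the correlation of 0.5 are all assumptions.

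Only secondary outcomes are affected. The sample size does not rest on them, and no primary conclusion changes. This is a cheap improvement, not an error that threatens the trial.

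**What to change.** Under Effectiveness of intervention, take mental health disorders out of the chi-square examples and state instead:

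- PHQ-9 and GAD-7 sum scores will each be compared between arms with a linear model, or a GEE model across visits, with the baseline score as covariate and robust standard errors because the scores are likely to be skewed.
- The four severity levels will be shown by arm and visit as descriptive results.
- One binary cut, fixed before outcome data are compared by arm, will be reported as a supportive analysis.

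Say in the same place that the GEE for these two outcomes uses the sum score, so that only one main analysis is on record.

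The cost is a change of wording. No new data, visits or participants are needed, because the sums are already computed and mental health is assessed at baseline. The downside is that a difference in mean score is less directly interpretable than a disorder rate; the rate is still reported beside it.

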**Methods:**

A non-blinded 1:1 parallel-group randomised controlled trial will be conducted in Guangzhou Eighth People’s Hospital, with 300 MSM enrolled in each arm. Eligible MSM who are newly initiating ART will be randomly assigned to an intervention group (standard-of-care case management plus mHealth intervention) or a control group (standard-of-care case management). The development of the mHealth intervention will be based on the information–motivation–behavioural skills theory of ART adherence, and comprise four components: educational articles, one-to-one online communication with case managers, support-service information and hospital-visit reminders. Outcome measures will be collected at baseline and at months 1, 3, 6, and 12. The primary outcomes will be ART adherence and CD4 count at month 6. Secondary outcomes include HIV RNA, sexual behaviours, mental health status, illness perceptions, and quality of life. *χ*^*2*^ test and t-test will be used for between-group comparisons. Intervention effects will be evaluated using General estimating equation performed by SAS 9.0, on the principle of intention-to-treat. Structural equation modelling will be used to test potential mechanisms of intervention effect.

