### Measures

#### Primary outcome

The primary outcome of this study is self-reported ART medication adherence and CD4 count at month six. As literature studies have shown that self-reported adherence is usually positively skewed, mostly due to social desirability bias and recall bias [45], we adopt a composite scale that has high sensitivity [46]. This scale consists of three adherence items measuring medication-taking adherence in the preceding 30 days: 1) a ‘days missed’ item, in which participants are asked the number of days they have missed an ART dose; 2) a ‘rating’ item, in which participants are asked to rate their pill-taking performance; 3) a ‘frequency’ item, in which participants are asked how frequently they took their pills according to instructions. Cronbach’s alpha was 0.86 in the previously reported study using this scale [47]. Moreover, item responses for the three adherence items were linearly transformed to a 0–100 scale and the average scores of all three items are used. A summary of the individual adherence items was calculated as the mean of the three individual items. In this study, we consider anyone scoring below the maximum score on any item as non-adherent (i.e., a combined scale score of < 100). CD4 counts are examined in each physical test and measured by flow cytometer. The months one and three assessments allow for trend evaluation and the month 12 assessments will allow for evaluation of persistent effect of intervention, but these are not the primary outcomes.

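### Month-6 CD4, a primary outcome, is assigned a t-test that ignores baseline, and the planned GEE is not said to adjust for baseline or to take priority

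*Protocol article*

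**What the plan says.** Under Effectiveness of intervention the article states: "The primary outcomes will be the prevalence of ART adherence and CD4 counts at month six". For comparisons between arms it gives a chi-square test for binary outcomes and a t-test "for continuous outcomes (e.g., CD4 count, quality of life, illness representation, IMB constructs, and HIV viral load". No covariate is named.

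On measurement, the Abstract (Methods) says: "Outcome measures will be collected at baseline and at months 1, 3, 6, and 12". The Primary outcome section adds: "CD4 counts are examined in each physical test and measured by flow cytometer".

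Two uses of baseline values are stated. Under Baseline comparison, a standardised difference above 0.1 is called imbalance, with no consequence for the analysis. Under Effectiveness of intervention: "Within-subject analyses will also be conducted, comparing the baseline response to follow-up session responses". The first describes the arms and the second looks within patients, so neither brings baseline into the comparison of outcome between arms.

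A second method is also planned. The Abstract says: "Intervention effects will be evaluated using General estimating equation performed by SAS 9.0". The Effectiveness section says the GEE "will be used for repeated measures analyses using SAS 9.0, which allows for the inclusion of all subjects in the analysis". Neither place says how baseline is handled in it, or whether it or the t-test is the primary analysis of month-6 CD4.

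For the PHQ-9 and GAD-7, the Secondary outcomes section says "the sum of all items will be calculated and categorized into different levels of mental health disorder", and mental health disorders are then listed among the binary outcomes for the chi-square test.

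**The concern.** When an outcome is also measured before randomisation, part of its spread at follow-up is spread that patients brought with them. A two-sample t-test on the follow-up value counts all of that as noise. An analysis with baseline as a covariate removes the part that baseline predicts, at no cost in patients or visits.

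Two things are at stake for CD4. The first is precision: the confidence interval for a primary outcome may be wider than the data require. This matters more because Sample size estimation gives power for adherence only, so CD4 has no stated power. The second is the realised estimate: if the arms happen to differ in baseline CD4, part of that difference stays in the unadjusted month-6 comparison. The plan checks for such imbalance but says nothing about acting on it. A decision to adjust taken after the check, in an open-label trial, would be post hoc.

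**Working it through.** **Inputs from the documents.** Sample size estimation gives 300 per arm, 20% attrition at month 6, two-sided alpha 0.05 and 80% power. The number analysed is taken as 300 × (1 − 0.20) = 240 per arm.

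**Assumption.** The baseline to month-6 correlation r is not in the documents. It is shown over 0.3 to 0.8. No CD4 standard deviation or target effect is given either, so differences are in units of the month-6 SD. For the same reason there is no CD4 power figure in the plan to reproduce.

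**Unadjusted t-test (normal approximation).** Detectable difference = (1.960 + 0.842) × √(2/240) = 2.802 × 0.0913 = 0.256 SD.

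**With baseline as covariate.** The variance is multiplied by 1 − r², so the detectable difference is 0.256 × √(1 − r²), and the unadjusted trial size giving the same precision is 240/(1 − r²) per arm.

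| Assumed r | Variance removed (r²) | Detectable difference | CI narrower by | Equivalent n per arm |
|---|---|---|---|---|
| none (t-test) | 0% | 0.256 SD | 0% | 240 |
| 0.3 | 9% | 0.244 SD | 5% | 264 |
| 0.5 | 25% | 0.221 SD | 13% | 320 |
| 0.7 | 49% | 0.183 SD | 29% | 471 |
| 0.8 | 64% | 0.153 SD | 40% | 667 |

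**The same in power terms.** For an illustrative true effect of 0.2 SD (not a figure of the plan), t-test power is Φ(0.2 × √120 − 1.96) = Φ(0.231) = 59%. With adjustment it is Φ(2.191/√(1 − r²) − 1.96), which is 63%, 72%, 87% and 95% for r = 0.3, 0.5, 0.7 and 0.8.

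**Chance imbalance.** With 300 per arm the standard error of a baseline standardised difference is √(2/300) = 0.0816, so chance alone gives a value beyond ±0.1 on a given variable with probability 2 × [1 − Φ(0.1/0.0816)] = 22%. A baseline CD4 difference of 0.1 SD shifts the unadjusted month-6 difference by r × 0.1 SD. At r = 0.5 that is 0.05 SD, or 0.05/0.0913 = 0.55 standard errors with 240 per arm. At r = 0.7 it is 0.07 SD, or 0.77 standard errors.

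**Why the planned GEE does not settle it.** The precision of its month-6 contrast depends on how baseline enters. Take complete data and equal SDs at both times:

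- Baseline as one more response, with free arm means at each visit: the month-6 contrast is the raw difference in means, variance factor 1.
- The arm-by-time term for month 6 against baseline: a comparison of change scores, factor 2(1 − r), that is 1.4, 1.0, 0.6 and 0.4 for r = 0.3, 0.5, 0.7 and 0.8.
- Baseline as covariate: factor 1 − r², that is 0.91, 0.75, 0.51 and 0.36.

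The text is compatible with all three.

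**The case against.** The strongest reply is that the t-test is only half of the plan. The Abstract assigns the evaluation of intervention effects to the GEE, and a repeated-measures GEE may well use baseline CD4. This stands as a limit: a reader might infer that an unadjusted t-test is the plan's only analysis of CD4, and the documents do not support that. It does not remove the point, because neither the handling of baseline in the GEE nor its priority is stated, and two of the three readings above give no baseline-covariate adjustment.

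Next, covariates are commonly left to a statistical analysis plan, and this is a condensed article. If the article only left the GEE's covariates unstated, there would be no finding. But it names a specific test for a primary outcome, and that test cannot use baseline. That is a stated choice, and a less efficient one than is available.

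Third, the t-test is valid. Under 1:1 randomisation it is unbiased and keeps its error rate, with chance imbalance already in its standard error. A reader might infer that imbalance biases the test. It does not: it adds variance and moves the one estimate that is observed, by r times the imbalance and not by all of it. Even given a baseline difference of 0.1 SD, the false-positive rate is 1 − Φ((1.96 − b)/s) + Φ((−1.96 − b)/s), with b the shift in standard errors and s = √(1 − r²). That is 5.3% at r = 0.5 and 4.7% at r = 0.7.

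Fourth, baseline CD4 is inferred. The list under Data collection does not name it, and the schedule (Table 3) is not shown. The Abstract's sentence cannot hold for every outcome, since patients not yet on treatment have no baseline adherence. This caveat stands. The Abstract together with CD4 testing at each physical test makes baseline CD4 likely but not certain.

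Finally, the categorising of PHQ-9 and GAD-7 concerns secondary outcomes and is no evidence about CD4. That is right; these scores come in only because the same remedy applies to them.

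**Conclusion.** The point holds as one of efficiency and of an unsettled primary analysis, not of validity. A primary outcome is given a test that ignores baseline, and the alternative analysis is not said to adjust for baseline or to prevail.

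The size depends on a correlation that the documents do not give: 9% to 64% of the variance over r from 0.3 to 0.8, or a detectable difference of 0.244 down to 0.153 SD in place of 0.256 SD. A reader might infer that most of the available precision is thrown away. That needs r² > 0.5, that is r > 0.707, and nothing in the documents establishes it; at 0.3, 0.5 and 0.7 the loss is below half.

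The figures rest on 240 analysed per arm, a normal approximation and a linear relation between baseline and month-6 CD4. The conclusion also needs baseline CD4 to be recorded. The change should be made, but a trial analysed as written would still give a valid CD4 comparison.

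**What to change.** 1. Name one primary analysis of month-6 CD4: an ANCOVA, or the month-6 contrast of the GEE already planned, with baseline CD4 as a prespecified covariate. State that it takes priority over the t-test.
2. Analyse the WHOQOL-HIV domain scores, the B-IPQ, the IMB scores and the PHQ-9 and GAD-7 sums in the same way, each with its own baseline value. Data collection lists these constructs at baseline.
3. Keep the unadjusted t-tests and the categorised mental health tables as descriptive support.
4. Confirm in the text that baseline CD4 is recorded for all participants.
5. Say that the covariate is used whatever the standardised-difference check shows.

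The cost is analysis wording only, settled before outcome data by arm are examined. If baseline CD4 is recorded as the text implies, no further data, visits or patients are needed.
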